**The secondary outcome measures include the following:**

**QoR-15 Score:** The QoR-15 score will be measured at baseline (before the surgery) and 4 and 6 weeks after surgery. The QoR-15 score is a patient-reported outcome questionnaire that measures the quality of postoperative recovery and fulfills the requirements for outcome measurement instruments in clinical trials.

**EPIC-26 Score:** The EPIC-26 score will be measured at baseline (before the surgery) and at 4 and 6 weeks after surgery.

**30-second chair-to-stand test:** The 30-second chair-to-stand test will be measured at baseline (before the surgery) and at 4 and 6 weeks after surgery.

**Clavien-Dindo complication system:** The Clavien-Dindo classification of surgical complications is a simple and widely used tool to assess and report postoperative complications in urologic surgery. The scores will be recorded at 4 and 6 weeks after the surgery.

**Operative:** Intraoperative surgical details will be recorded to compare telesurgery and local surgery. The conversion rate, operative blood transfusion rate, intraoperative blood loss, operative time, and warm ischemia time (for partial nephrectomy) will be recorded.

**Postoperative:** The postoperative conditions of the patients can reflect the effects and success of the surgery. Postoperative hospitalization days, length of days in critical care, reoperation intervention, the postoperative blood transfusion rate, and the mortality rate will be recorded through the clinical information system.

**Oncological outcomes:** The oncological outcomes for prostate cancer and renal cancer patients are key factors in the prognosis. After the surgery, the cancer sample will be viewed by two blinded pathologists.

The surgical margin rate will be focused.

### 3.7 End of Study

The end of study would be the last patient, last follow up clinic appointment.

## 4 STUDY SCHEDULE

[figure not shown]

## 5 TABLE OF ASSESSMENTS

| Items

Period                                      | Screening | Surgery                    | Follow-up       |                 |
|----------------------------------------------------------|-----------|----------------------------|-----------------|-----------------|
|                                                          | Visit 1   | Visit 2                    | Visit 3         | Visit 4         |
|                                                          | -7~0 day  | Surgery day
0 day~3 day | 4 weeks ±3 days | 6 weeks ±3 days |
| Screening/grouping                                       | ●         |                            |                 |                 |
| Informed consent &
randomisation                      | ●         |                            |                 |                 |
| Fill in the basic
information             | ●         |                            |                 |                 |
| Take medical
history                      | ●         |                            |                 |                 |
| Vital signs
examination                               | ●         | ●                          | ●               | ●               |
| Blood routine
examination                 | ●         | ●                          | ●               | ●               |
| Biochemical
examination                   | ●         | ●                          | ●               | ●               |
| Routine urine
examination                 | ●         |                            |                 |                 |
| Coagulation function                         | ●         |                            |                 |                 |
| Preoperative
pathological report          | ●         |                            |                 |                 |
| Electrocardiogram
examination             | ●         |                            |                 |                 |
| Chest CT/ X-ray                              | ●         |                            |                 |                 |
| Lesion location
CT/MR                     | ●         |                            |                 |                 |
| Whether the operation
was successful or not           |           | ●                          |                 |                 |
| Operation time                                           |           | ●                          |                 |                 |
| Blood loss volume                                        |           | ●                          |                 |                 |
| Blood transfusion
volume                              |           | ●                          | ●               |                 |
| Surgery conversion                                       |           | ●                          |                 |                 |
| Task load of the
medical team                         |           | ●                          |                 |                 |
| Telesurgery system
monitoring indicators  |           | ●                          |                 |                 |
| Length of days in
hospital                            |           |                            | ●               |                 |
| ICU time                                                 |           |                            | ●               |                 |
| Positive margin of
tumor sample           |           |                            | ●               |                 |
| 30 second chair to
stand test             | ●         |                            | ●               | ●               |
| QoR-15 scale                                             | ●         |                            | ●               | ●               |
| EPIC-26 Scale                                            | ●         |                            | ●               | ●               |

|                                                    |  |   |   |   |
|----------------------------------------------------|--|---|---|---|
| Complication                                       |  | ● | ● | ● |
| Re-hospitalizations
and emergency
operations |  | ● | ● | ● |
| Mobility                                           |  | ● | ● | ● |
| Instrument
malfunction                          |  | ● |   |   |
| Record adverse events                              |  | ● | ● | ● |

1. These preoperative examinations will be performed by the medical system at the trial sites.

2. Preoperative pathological reports for patients with prostate cancer will be collected by the medical system at the trial sites or via paper reports from other hospitals.

3. The status of the surgical margin will be collected by the pathological report of the tumor, which is reviewed by one or two blinded pathologists.

4. The 30-s chair-to-stand test at baseline will be tested by the nurse before the surgery. In the follow-up period, this test will be performed in the outpatient service by the doctor. If the patients cannot go to the surgery hospital, this test will be performed by the follow-up nurse via WeChat (A widely popular social app in China that can perform various operations such as questionnaire investigation, voice and video).

5. The monitoring status of the telesurgery system will be collected by the telesurgery technique team.

## 6 PATIENT SCREENING & CONSENT

### 6.1 Patient Screening

During the patient screening period in each trial center, newly admitted or outpatient patients diagnosed with renal tumors or prostate cancer will be included in the screening. The patient information included in the screening will be naturally archived according to the clinical information system. Patients who meet the eligibility criteria for this clinical trial will be invited to participate.

### 6.2 Informed Consent

Patients who have been informed of their cancer diagnosis and approached about the suitability of robot-assisted partial nephrectomy or prostatectomy may be invited to participate in this trial.

It is the responsibility of the investigator to obtain written informed consent from (ICF) each patient prior to their entry into the study and before assessments that are not conducted as part of standard care are performed. A patient information sheet and ICF will be provided to facilitate this process. The investigator or their designee must ensure that they adequately explain to the patients the aims of the study, the study schedule, and follow-up visits, and that this study is a randomized controlled trial. At the same time, patients will be informed that the surgery will be performed by a Chinese robotic surgery system that has been registered with the Chinese Food and Drug Administration (CFDA). Patients should be informed that the surgery will be performed via telesurgery or normal local surgery.

The investigator or their designee will also inform patients that their participation is voluntary and that they can withdraw from the study at any time without it affecting their standard of care.

Patients will be given ample time and opportunity to inquire and ask questions about the trial and to decide whether or not to participate. The right of patients to refuse to participate in the trial, with or without giving

a reason, will be respected.

If a patient expresses an interest in participating in the study, they will be asked to sign and date the REC (Research Ethics Committee)-approved version of the ICF in the presence of the investigator, who will then co-sign and date the form. The patient will personally initial all boxes. A copy of the ICF will be given to the patient, a copy will be filed in the hospital notes, and the original will be placed in the investigator site file and mail to Chinese PLA General Hospital, when this trial is finished. A dated annotation will be made in the patient's medical notes stating that consent has been given, with the name of the trial and the version numbers of the ICF. Throughout the study, the patient will have the opportunity to ask questions about the study and any new information that may be relevant to the patient's continued participation.

By providing informed consent, participants will be consenting for the study to conduct follow-ups and collect their data.

### **6.3 Withdrawals**

As participation in the study is entirely voluntary, participants may choose to discontinue at any time during this trial without penalty or loss of benefits to which they would otherwise be entitled.

## **7 ELIGIBILITY CRITERIA**

### **7.1 Inclusion Criteria**

Participants will have to meet the following criteria for inclusion in the study: (1) age, 18–80 years; (2) body mass index, 18–30 kg/m^2; (3) fit to undergo urologic laparoscopic surgery, including prostatectomy and partial nephrectomy; (4) physiological condition suitable for robot-assisted laparoscopic surgery; (5) willingness to cooperate and complete study follow-up and related examinations.

## **7.2 Exclusion Criteria**

Participants who meet any of the following criteria will be excluded: (1) severe cardiovascular or circulatory diseases that are not tolerable for surgery; (2) pregnancy or lactation; (3) history of epilepsy or mental illness; (4) severe allergies or suspected/confirmed alcohol or drug addiction; (5) inability to understand study requirements or complete the study's follow-up schedule.

## **8 RECRUITMENT**

All patients who have a diagnosis of renal tumor or prostate cancer and for whom partial nephrectomy or prostatectomy is recommended as a treatment option may be approached. It is important to keep patient withdrawals from the study to a minimum; however, a patient may withdraw from the study at any time without prejudice to their subsequent treatment.

In this randomized trial, all participants will be randomized to either

arm A (telesurgery group) or arm B (local surgery group).

## 9 STATISTICAL METHODS

### 9.1 Study Analysis

This section highlights the statistical considerations for this protocol. More details about statistical analysis are provided in a separate *Statistical Analysis Plan* document.

### 9.2 Sample Size Determination

According to the requirements of the "Guideline for the Design of Clinical Trials of Medical Devices" (published by CFDA), the number of trial cases was inferred based on the non-inferiority sample size calculation method, and the number of cases was calculated through joint discussion by clinical trial institutions, major researchers, and statistical analysts.

The formula is as follows:

$$n_T = n_C = \frac{(Z_{1-\alpha/2} + Z_{1-\beta})^2 [P_C(1-P_C) + P_T(1-P_T)]}{(|D| - \Delta)^2},$$

where  $\alpha = 0.025$  (one-sided),  $\beta = 0.2$  (80% confidence), and the non-inferiority margin  $\Delta = 10\%$ . Assuming that the surgical success rate of the experimental group and the control group is equal, the expected surgical success rate of the two groups is 98% (i.e.,  $P_T = P_C = 98\%$ ). As the ratio between the two groups is 1:1, 31 subjects are needed in each group.

Considering that the dropout rate of subjects during the trial is about 10% or more, this study plans to enroll 68 subjects, with 34 in the experimental group and 34 in the control group. If the dropout rate exceeds the expected 10%, resulting in insufficient valid cases, the number of participants can be appropriately increased, and the number of the total valid cases should not be higher than 34 of each trial group. The increase in the number of patients enrolled should be filed with the Ethics Committee of Chinese PLA General Hospital.

Urologic surgery is divided into upper and lower urinary tract surgeries. In this clinical trial, representative surgical methods of partial nephrectomy and prostatectomy are selected for surgery. In the end, partial nephrectomy and prostatectomy in this scheme is no less than 30%, and each clinical center ensures that subjects are operated on for both partial nephrectomy and prostatectomy surgery. This information will be summarized after the end of the trial. According to the non-inferiority test, when the lower limit of the 95% confidence interval of the difference in surgical success rate between the two groups is  $> -10\%$ , the non-inferiority hypothesis is established, which can be considered to meet the qualified requirements of this clinical trial.

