### 3.2 Sample Size

According to the requirements of the "Guideline for the Design of Clinical Trials of Medical Devices" (published by CFDA), the number of trial cases was inferred based on the non-inferiority sample size

calculation method, and the number of cases was calculated through joint discussion by clinical trial institutions, major researchers, and statistical analysts.

The formula is as follows:

$$n_T = n_C = \frac{(Z_{1-\alpha/2} + Z_{1-\beta})^2 [P_C(1-P_C) + P_T(1-P_T)]}{(|D| - \Delta)^2},$$

where  $\alpha = 0.025$  (one-sided),  $\beta = 0.2$  (80% confidence), and the non-inferiority margin  $\Delta = 10\%$ . Assuming that the surgical success rate of the experimental group and the control group is equal, the expected surgical success rate of the two groups is 98% (i.e.,  $P_T = P_C = 98\%$ ). As the ratio between the two groups is 1:1, 31 subjects are needed in each group. Considering that the dropout rate of subjects during the trial is about 10% or more, this study plans to enroll 68 subjects, with 34 in the experimental group and 34 in the control group. If the dropout rate exceeds the expected 10%, resulting in insufficient valid data, the number of patients enrolled can be appropriately increased, and the proposed increase in the number of patients enrolled should be filed with the Ethics Committee of Chinese PLA General Hospital.

Urologic surgery is divided into upper and lower urinary tract surgeries. In this clinical trial, representative surgical methods of partial

nephrectomy and prostatectomy are selected for surgery. In the end, partial nephrectomy and prostatectomy in this scheme is no less than 30%, and each clinical center ensures that subjects are operated on for both partial nephrectomy and prostatectomy surgery. This information will be summarized after the end of the trial. According to the non-inferiority test, when the lower limit of the 95% confidence interval of the difference in surgical success rate between the two groups is  $> -10\%$ , the non-inferiority hypothesis is established, which can be considered to meet the qualified requirements of this clinical trial.

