## **8.3 Efficacy analysis**

### **8.3.1 Primary outcome analysis**

The primary outcome will be analyzed by a non-inferiority analysis. According to the medical statistics scenario, the main efficacy evaluation is based on the intention-to-treat population set and per-protocol population set. The statistical description and inference will be based on the characteristics of the data, and the appropriate descriptive indicators and hypothesis testing methods will be selected.

The primary efficacy indicator of surgical success rate uses a non-inferiority test, with the following hypotheses tested:

Null hypothesis:  $H_0: PT - PC \leq -\Delta$ ;

Alternative hypothesis:  $H_1: PT - PC > -\Delta$ .

At  $\alpha = 0.025$  (one-sided test) and  $\beta = 0.2$  levels, the success rates of the two groups will be statistically described and compared, and the 95% confidence interval (CI) of the difference in success rates between the two groups will be calculated. If the lower limit of the 95% CI of the difference in success rates between the two groups is greater than the non-inferiority margin ( $-\Delta$ ), it can be concluded that the experimental group is non-inferior to the control group.

The difference in the primary outcome (success rate) between the telesurgery and local surgery groups will be compared using the Miettinen-Nurminen method or Newcombe-Wilson score method test, according to the success rate data. The tipping assay can be used to determine the robustness and sensitivity the statistical conclusion.

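### The 80% power comes from a normal approximation that the primary analysis does not use; under the interval methods named in the SAP, power at 34 per group is about 30%

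*Combined protocol and SAP*

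**What the plan says.** Protocol 9.2 and SAP 3.2 give the same sample size derivation. Both set alpha at 0.025 one-sided, beta at 0.2 and the margin at 10 percentage points, with 98% success assumed in each arm. Both use the unpooled normal-approximation formula for a difference in proportions. The result is "As the ratio between the two groups is 1:1, 31 subjects are needed in each group", and after allowing for about 10% dropout "this study plans to enroll 68 subjects, with 34 in the experimental group and 34 in the control group".

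The protocol allows extra enrolment if dropout exceeds 10%, but adds that "the number of the total valid cases should not be higher than 34 of each trial group". SAP 3.2 allows the increase without that limit.

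The criterion in both sections is met "when the lower limit of the 95% confidence interval of the difference in surgical success rate between the two groups is" above -10%. SAP 8.3.1 repeats the rule and says that the success rates will be compared "using the Miettinen-Nurminen method or Newcombe-Wilson score method test, according to the success rate data". Neither document reports power for those methods.

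**The concern.** The formula that sizes the trial and the interval that decides it are different methods. They differ most when success is close to 100%, which is the assumed setting. At 98% success and 34 patients, 34 × 0.02 = 0.68 failures are expected per arm. With so few events an estimated normal variance is unreliable and collapses to zero when no failure is seen. The score-type limits keep a realistic width there, so they are much harder to bring above -10%.

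The criterion determines whether the trial is regarded as having met its requirements. If the true power is far below 80%, the likeliest outcome under the sponsor's own assumption of equal 98% success is that non-inferiority is not shown. Readers who were told 80% could take that as a sign that telesurgery is worse.

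**Working it through.** **Inputs.** Success 98% in each arm, margin 0.10, alpha 0.025 one-sided (z = 1.960), beta 0.2 (z = 0.8416), 1:1 allocation, 31 evaluable and 34 enrolled per group (protocol 9.2, SAP 3.2). Pass rule: lower limit of the two-sided 95% interval above -10%, by Miettinen-Nurminen (MN) or Newcombe-Wilson (SAP 8.3.1).

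**1. The plan's own figure.** n = (1.960 + 0.8416)² × (2 × 0.98 × 0.02) / 0.10² = 30.8, so 31. It reproduces when the printed Z(1-α/2) is read as 1.960. Dropout: 31 / 0.9 = 34.4, against 34 stated.

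**2. No failures in either arm.**

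- Newcombe: the Wilson lower limit for n successes out of n is n / (n + z²), with z² = 3.8415. The lower limit for the difference is therefore -3.8415 / (n_T + 3.8415), where n_T is the size of the telesurgery arm.
- MN: at a difference of -0.10 the constrained estimates are 0.90 and 1.00. The statistic is 0.10 / √[(0.09 / n_T) × N/(N-1)], where N is the total, and it must exceed 1.960.

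| Per group | Newcombe lower limit | MN statistic | MN lower limit |
|---|---|---|---|
| 34 | -10.15% (fails) | 1.929 | -10.29% (fails) |
| 35 | -9.89% (passes) | 1.958 | -10.02% (fails) |
| 36 | -9.64% (passes) | 1.986 | -9.76% (passes) |

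**3. Which results pass at 34 against 34.** Full enumeration gives the same region for both methods over the outcomes that matter:

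| Telesurgery failures | Local failures needed to pass |
|---|---|
| 0 | at least 1 |
| 1 | at least 2 |
| 2 | at least 4 |

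No tie passes by either method, and no result in which telesurgery has more failures passes.

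**4. Exact power at 98%/98%, 34 per group.** The binomial probabilities of 0, 1, 2 and 3 failures in an arm are 0.5031, 0.3491, 0.1176 and 0.0256, which leaves 0.0046 for 4 or more. Then:

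- 0 against at least 1: 0.5031 × 0.4969 = 0.2500
- 1 against at least 2: 0.3491 × 0.1478 = 0.0516
- 2 against at least 4: 0.1176 × 0.0046 = 0.0005

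The sum is 0.302; further terms are negligible.

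**5. Other sizes and rates, by the same enumeration.**

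| Per group | MN | Newcombe |
|---|---|---|
| 31 | 25.7% | 25.7% |
| 34 | 30.2% | 30.2% |
| 35 | 30.5% | 54.8% |
| 36 | 54.1% | 54.1% |
| 40 | 51.6% | 51.6% |
| 59 | 75.1% | 83.0% |
| 60 | 82.6% | 82.6% |

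At 34 per group, a true 99% in both arms lowers power to 21.7%, and a true 100% lowers it to 0%. Under the assumed 98%, the chance of no failure among 68 patients is 0.98^68 = 25%.

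**6. The interval that matches the formula.** A Wald interval would show 85.6% power at 34 per group. It also passes 34/34 against 34/34 and 33/34 against 34/34. If the true rates were 90% and 100%, its false-positive rate would be 0.9^34 + 34 × 0.1 × 0.9^33 = 0.028 + 0.105 = 13.3%, against a nominal 2.5%.

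**The case against.** **The formula is standard and correctly evaluated.** That is true, and a reader might infer from the mismatch that 31 is a calculation error. It is not. The 80% belongs to an approximation that is poor here and that SAP 8.3.1 does not use.

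**Not every flawless trial fails.** A reader might infer that 100% success in both arms can never pass. The documents do not support that. The failure is exact for 34 against 34, and the result turns on the size of the telesurgery arm. SAP 3.3 randomises in blocks of four within two strata, which does not force equal arms. At 36 telesurgery against 32 local patients an all-success result passes by both methods (power 53.1%); at 35 against 33 it passes by Newcombe only (54.3%). The cap stands only in the protocol and limits valid cases, while the ITT set in SAP 6.1 is everyone randomised, so replacing dropouts could take an arm past 34. All of this stands, but at these sizes power is still only about 53% to 55%.

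**The SAP calls the trial exploratory.** It does, in section 3. Protocol 9.2 and SAP 8.3.1 nevertheless set a pass/fail rule with a stated beta, and the label does not make that beta true.

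**The cap could simply be deleted.** That is tempting, since an all-success result first passes at 35 or 36. But protocol 3.3 says that researchers are not blinded, and protocol 3.6 fixes the primary outcome at the end of each operation. Enrolment with no upper limit would be open to decisions made on known results. Power also does not rise steadily with size, so a few patients either way matter.

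**Conclusion.** The concern holds. The stated 80% is not the power of the planned analysis. Under either named method it is about 26% at 31 per group and 30% at 34, and at 34 against 34 the criterion can be met only when telesurgery shows strictly fewer failures than local surgery. An all-success result passes only with at least 35 (Newcombe) or 36 (MN) telesurgery patients. About 60 per group would be needed for 80%.

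These figures assume complete data, 98% success in both arms, equal arms unless stated, the MN interval with its N/(N-1) factor, and the Newcombe interval without continuity correction. Dropping the N/(N-1) factor leaves 30.2% unchanged; a continuity-corrected Newcombe interval would lower it to 8.5%. The multiple imputation in SAP 6.1 was not modelled, and the SAP specifies no stratified interval for the primary outcome.

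**What to change.** In protocol 9.2 and SAP 3.2:

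1. Name one interval method in advance, and replace the 80% with its exact power at the planned size: about 30% at 34 per group, 26% at 31. Carry the same choice into SAP 8.3.1, in place of a choice made according to the data. The choice matters: at 35 per group the two methods give 30.5% and 54.8%.
2. State which results can meet the criterion at that size, and that failing to meet it will not be read as evidence of inferiority.
3. Record that about 60 per group would be needed for 80% under the same assumptions, so that the sponsor decides on size knowingly.
4. Reconcile the cap, which the protocol has and the SAP lacks, by pre-specifying one fixed maximum per group with its exact power.

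The cost is amended wording in both documents and a much less favourable stated power. More enrolment is not needed to correct the figure; whether to enrol more is a separate decision for the sponsor.
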